### Sample

The combined multi-level sample for both studies will include 74 programs/districts, 74 agency/district leaders (1 per agency/district), 590 providers (average of 8 per program/district), and 590 children (1 per provider). This sample size was determined so as to be sufficiently powered for aim 3 mediation analyses. (Refer to Table 1 for the breakdown of participants by study and type).

**Table 1 Tab1:** Participants by type and study

AIM HI study (37 MH programs)	CPRT study (37 school districts)	Combined (74 agencies)
37 Program managers	37 Program specialists	74 Leaders
295 Therapists	295 Teachers	590 Providers
295 Clients	295 Students	590 Children
*627 Total AIM HI*	*627 Total CPRT*	*1254 Total Combined*

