#### Outcome measures

Because we are testing an implementation intervention and our ASD EBI have been shown to be effective in our large-scale effectiveness trials, our primary measures are related to provider implementation (training completion/fidelity). However, consistent with Hybrid, type 3 designs, we will collect child outcome data as secondary outcome measures (within session behavior; standardized measures). Outcomes will be collected for leaders and providers using the following timeframes: Baseline (BL—initial program/district enrollment), Pre (PRE—prior to EBI Training), Post training (POST—6 months after initiation EBI training), and Follow-Up (12 months post PRE). Parents will complete child measures at PRE and POST as children may not remain with the same provider or be receiving services at follow-up. Data will be collected by administering a brief battery of measures (including demographic measures for all participants) via on-line survey or phone interview. The outcome constructs include implementation outcomes (provider and child) as well as measurement of the specific mechanisms of change expected from the implementation intervention. Refer to Table 3 for specific outcome measures and timing.

**Table 3 Tab3:** Study measures

Purpose (aim)	Construct	Measure/indicators	Timeframe			
			BL	Pre	Post	FU
Outcomes (aim 1)	Training completion	Provider training/consultation completion (based on trainer-rated attendance tracking)			X	
	Provider fidelity	Fidelity of ASD EBI (*also collected mid-training for total of 3 obs.*)		X	X	.
	Child improvements	Child session behaviors (disruptive, engagement)		X	X	
		Child symptom improvement (ECBI [AIM HI]/PDDBI [CPRT])		X	X	
Mechanisms of change (aims 2, 3)	Provider engagement	Training/consultation attendance (trainer rated)			X	
		Adherence to training requirements (video submissions, forms)			X	
	Provider attitudes	Evidence-Based Practice Attitudes Scale (EBPAS)		X	X	X
		Adapted motivation inventory [116]		X	X	X
	Impl. Leadership & Climate	Implementation Leadership Scale (leaders and providers) [98]	X	X	X	X
		Implementation Climate Scale [117] (leaders and providers)	X	X	X	X
	Implementation support use	Assessment of implementation supports strategies	X	X	X	X
Moderators (aim 3)	Background/experience	AIM HI & CPRT Background Questionnaire (leaders & providers)	X (L)	X (P)		
	Org. structure	Program/District Structure Questionnaire	X			

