#### Provider fidelity measures

Provider ASD EBI (AIM HI/CPRT) fidelity is the primary study outcome. Provider fidelity will be based on ratings by trained observers blind to study condition and time frame. Fidelity ratings are designed to capture provider use of the core EBI strategies included in the AIM HI and CPRT protocols. Fidelity will be rated with the target child at PRE, mid training, and POST. Fidelity will be coded based on video recordings of sessions/activities using our established procedures for video data collection. AIM HI Fidelity includes 16 Adherence items reflecting expected within-session therapist behaviors in three categories (Structuring Sessions for Skill-Building, Motivating Children, Active Teaching). These are rated separately for parents and children. There are also 4 Effectiveness Items (e.g., session is organized and structured). The inter-rater reliability of these items are high (*M* = .77, range = 0.65 to 0.90 based on 299 double-coded sessions). Furthermore, all individual and composite scores for therapists trained in AIM HI are significantly higher than therapists delivering usual care (based on over 600 coded sessions), providing support for the discriminant validity of the measure. Sessions recordings will be submitted online prior to training and monthly during the 6-month training/consultation period*.* CPRT fidelity includes 15 adherence items reflecting expected within-session teacher behaviors in three categories (maximizing student motivation, facilitating student responding, providing appropriate consequences). There are also 4 effectiveness items (e.g., manages distractions in the teaching environment). All items are rated on a 1–5 Likert scale after observing the complete activity with 1 being teacher does not implement or implements correctly less than 30% of the time to 5, teacher implements correctly throughout the session (100%). The inter-rater reliability of these items are high (*M* = .73, range = 0.50–0.90 based on 240+ double-coded sessions).

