## Data analysis

### General data analytic plan for aims 1–3

All data analytic strategies will follow the recommendations of Brown et al. and the Prevention Science and Methodology Group for randomized field trials [103]. Preliminary data screening and cleaning will require examination of the data distributions for normality and missing data patterns at both the univariate and multivariate level. Preliminary data analysis will also be conducted to determine if there are significant differences between the two studies (CPRT and AIM HI) on target variables. If no significant differences are found, data from the two studies will be integrated to maximize the available data for specific analyses. In the case that outcome variables differ by study, variables representing study will be included as a covariate in all models. Some of the target outcome variables in the two studies were measured using different scales (e.g., AIM HI and CPRT Fidelity). To ensure comparability on these measures, variables will be converted to *z*-scores before statistical comparisons are made. Hierarchical linear modeling (HLM) will be used as the primary, but not only, statistical model due to the nested structure of the data and when the outcome measure is at the provider/outcome level: repeated measures [level-1] nested within providers/children [level-2] nested within program/district [level-3]). Possible clustering effects will initially be estimated by examining intraclass correlation coefficients to determine if accounting for clustering is necessary. All analyses will use an intent-to-treat approach for the TEAMS groups. Because the TEAMS condition variable will contain four groups, three dummy-coded variables will be created and used as predictor variables in target statistical models. To account for the different type of leader at the program/district level, a level-3 binary variable representing whether or not the agency/district leader is a director or a first-level leader will be used in all analyses. Covariates (e.g., baseline scores) may be included in the models to adjust for nonequivalence at baseline and to minimize bias. All analyses will use AR(1) to model a first-order autoregressive correlation structure for the repeated-measures data. Missing data common to longitudinal designs is readily incorporated in HLM if the data can be assumed to be missing at random. However, because there is no statistical test of data that is missing at random [104], all data analysis will also employ selection models [105] to model relationships of interest for the data missing not at random mechanism, as recommended by Little and Rubin [106]. Of interest in some of proffered hypotheses are the differences in target outcomes between the TEAMS groups over time. The TEAMS groups will be statistically compared when a significant cross-level (Time X TEAMS Group) interaction is evident using the statistical methods of Preacher, Curran, and Bauer [107].

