
#### Specific analyses for aim 1: test the effectiveness of the TEAMS modules individually and in combination on implementation outcomes when paired with two ASD EBI

To determine if there are significant main effects and interactions between the TEAMS groups on observed therapist fidelity (based on video recorded sessions coded at 3 time points over 6 months), statistical analyses will proceed using the 3-level nested data structure outlined in the General Analytic Plan section. To determine if there are significant differences between the TEAMS groups on observed child behaviors during sessions, statistical analyses will proceed using the 3-level nested data structure outlined in the General Analytic Plan section. To determine if there are differences between the TEAMS groups on child symptoms (EBCI or PDDBI) at 6 months, the 3-level nested data structured will be used.

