### Power analyses

To estimate the sample size needed to detect statistically significant differences between TEAMS groups in the context of the 3-level nested data structure (e.g., aim 1, hypothesis 1), the power program RMASS2 [109] was used. The RMASS2 program is specifically designed to calculate the projected sample size needed for longitudinal data with attrition when a comparison is made between groups. To determine the minimum sample size necessary, several assumptions were made: (1) An alpha level of .05 and a power level of 0.80, (2) an effect size of *d* = .39 (based on the CPRT effectiveness trial ES for impact of training on teacher fidelity), (3) 30% overall attrition rate was specified, and (4) a stationary autoregressive structure (lag 1) was specified for the variance-covariance matrix of the repeated measures, using an autocorrelation value of 0.60. In addition, clustering at the programs/districts level was accounted for via the variance inflation factor (VIF = 1.28): 1 + (*c* − 1) × ICC, where *c* is the average number of providers/children per programs/districts (*n* = 8) and the ICC at the programs/districts level (ICC = 0.04, based on AIM HI therapist fidelity outcome). Given these assumptions, 502 providers/children nested within 63 programs/districts are needed to detect statically significant differences between at least two of the TEAMS intervention groups.

Additional power analyses were conducted to determine the sample size needed to detect a hypothesized mediated effect or moderation of the antecedent to mediator relationship (see Aim 3), which is likely to be the most underpowered effect proposed. This set of power analyses was conducted to determine the minimum necessary sample size to find a statically significant mediated effect from variables presenting the TEAMS groups to a target mediator (e.g., provider attitudes) to a target outcome (e.g., provider fidelity outcome). Using the simulation approach for meditational models of Thoemmes, MacKinnon, and Reiser [110], small effects (*R*^2^ values of 2%) were specified for both the mediator and outcome variables. Accounting for the VIF defined above, 591 providers/children nested within 74 programs/districts are needed to detect statistically significant mediated effect.

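### The blanket AR(1) rule does not fit the two-occasion child outcomes and, in its usual form, assumes for fidelity a constant variance across the start of training that nothing in the article supports

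*Protocol article*

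**What the plan says.** The general data analytic plan fixes the covariance rule: "All analyses will use AR(1) to model a first-order autoregressive correlation structure for the repeated-measures data". The same section sets the model levels as "repeated measures [level-1] nested within providers/children [level-2] nested within program/district [level-3". The aim 1 section applies that structure to observed fidelity, to child session behavior and to child symptoms; for symptoms it speaks of "differences between the TEAMS groups on child symptoms (EBCI or PDDBI) at 6 months, the 3-level nested data structured will be used".

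The Outcome measures section and Table 3 give the occasions. Both child outcomes are collected at PRE and POST only. Fidelity is rated at PRE, mid-training and POST, and PRE comes before EBI training. The Sample section plans "590 children (1 per provider"), so provider and child are the same unit at level 2.

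The Power analyses section uses the same family of structure: "a stationary autoregressive structure (lag 1) was specified for the variance-covariance matrix of the repeated measures, using an autocorrelation value of 0.60".

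**The concern.** A single covariance rule is applied to outcomes with different numbers of occasions and different histories.

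With two occasions and one child per provider, a level-2 random effect and a serial correlation describe the same thing: the association between PRE and POST. If both are fitted, the software is asked to split one quantity in two, and the analyst must depart from the rule.

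For fidelity, the primary outcome, PRE records practice before training and the other two ratings come during and at the end of training. The spread between providers may well change over that step, and ratings on either side of it may correlate less than two ratings after it. The usual AR(1) allows neither. Model-based standard errors follow the imposed structure. If POST is more variable than the pooled variance, an arm difference at POST looks more precise than it is. If POST is less variable, the test is too conservative.

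**Working it through.** **The plan's own figure.** Take the time-averaged difference between two groups under stationary AR(1), rho = 0.60, three occasions, d = 0.39, two-sided alpha 0.05 (sidedness assumed) and power 0.80.

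- 1'R⁻¹1 = (3 − 0.60)/(1 + 0.60) = 1.5
- n per group = 2 × (1.96 + 0.842)² / (1.5 × 0.39²) = 68.8
- 4 groups × 68.8 × VIF 1.28 / (1 − 0.30) = 503, against 502 stated

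The stated size is reproduced with AR(1) alone within provider plus a VIF for programs/districts. No sample-size error follows from this point.

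**Two occasions.** Let t be the provider/child variance, s the residual variance and rho the autocorrelation. Then Var = t + s and Cov = t + rho·s. These are two moments for three parameters, and the Jacobian has rank 2. For example, (t, s, rho) = (0, 1, 0.6), (0.3, 0.7, 0.43) and (0.6, 0.4, 0) all give Var = 1 and Cov = 0.6. With one child per provider there is no other replication to separate them. With three occasions the rank is 3, so fidelity does not have this problem. For a non-negative PRE-POST correlation, dropping either term leaves the same 2×2 covariance, and so the same arm estimate and standard error.

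**Unequal variances: method.** The article gives no SD by occasion, so the PRE/POST SD ratio is an assumption, varied from 0.5 to 1.25. The true structure was AR(1) correlation with rho = 0.60 and unequal SDs, with the mid-training SD halfway between PRE and POST. The best-fitting equal-variance AR(1) was found in large samples, leaving out the program/district level. With k = model SE / true SE, the actual two-sided error is 2[1 − Φ(1.96k)].

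**Two occasions, complete data.** The equal-variance fit pools the variances, so at POST k = √[(r² + 1)/2] for SD ratio r. At r = 0.75, k = √0.78125 = 0.884, which gives 8.3%. For PRE-to-POST change, k = 1 at every r, because pooling preserves the sum of the two variances and the covariance.

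**Fidelity, three occasions (numerical fit).**

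| PRE/POST SD | POST, complete | POST, 30% monotone dropout | PRE-to-POST change, complete | Change, 30% dropout |
|---|---|---|---|---|
| 0.5 | k 0.78, 12.6% | k 0.75, 14.4% | 6.1% | 8.4% |
| 0.75 | k 0.88, 8.4% | k 0.86, 9.1% | 5.2% | 6.2% |
| 0.9 | k 0.95, 6.2% | k 0.94, 6.4% | 5.0% | 5.4% |
| 1.0 | k 1.00, 5.0% | k 1.00, 5.0% | 5.0% | 5.0% |
| 1.25 | k 1.13, 2.7% | k 1.15, 2.5% | 5.1% | 4.4% |

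**Other assumed true structures (complete data).** SDs 0.6/0.9/1.0 with correlations 0.3 (PRE-mid), 0.3 (PRE-POST) and 0.6 (mid-POST) give k = 0.847 and 9.7% at POST, with or without a provider intercept. SDs 0.7/1.0/1.2 with the same correlations give 10.7%. Equal SDs with correlations 0.2, 0.2 and 0.7 leave POST at 5% but give 10.4% for mid minus PRE and 0.8% for POST minus mid. Over all complete-data scenarios tried, PRE-to-POST change stays at about 3% to 6%.

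**After the change.** When variances may differ by occasion, k at POST returns to 1.00 in the SD-ratio scenarios of the table.

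**The case against.** The AR(1) sentence fixes a correlation structure and does not mention variances. Stationarity is stated only in the power section. Heterogeneous-variance AR(1) would satisfy the sentence as worded. This stands: equal variance is the usual reading of AR(1) and agrees with the power section, but the analysis text does not impose it.

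No equation adds a provider intercept to AR(1), and the power figure is reproduced without one. AR(1) alone is identified on two occasions. This also stands, so the redundancy is conditional on fitting the stated level 2 as a random effect. A reader might infer that the two-occasion models will fail to converge, or that the redundancy makes their error bars wrong. Neither follows: failure to converge is not shown, and inference is the same whichever term is removed.

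The SDs and correlations are assumed. The share of 27–30% of providers not meeting fidelity criteria (Background) is a proportion and does not show that variance rises after training. The low anchor, "1 being teacher does not implement or implements correctly less than 30% of the time", belongs to individual CPRT items and does not establish a floor in a composite, and no AIM HI anchors are given. The direction is therefore open, as the last row of the table shows. Conversion to z-scores would remove the variance issue only if done within each occasion, which is not stated.

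The plan compares groups once the Time x Group interaction is significant, and the PRE-to-POST contrast is nearly immune. A reader might infer that the main fidelity test is inflated to about 10%; the calculations do not support that. POST-only contrasts can still arise as follow-up comparisons, and the child-symptom question is posed at 6 months.

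A reader might also extend the point to every outcome or to leadership and climate. The sentence covers repeated measures only, and training completion is recorded once. The aim 2 section allows single-level regression with baseline control and does not say that the 6- and 12-month scores are modelled jointly.

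Details of covariance modelling are often left to the analysis plan. Here, however, the article fixes a rule for all analyses, so its fit to the listed outcomes can be judged.

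**Conclusion.** The point holds in limited form. For child session behavior and child symptoms, AR(1) together with a provider/child random effect is redundant. This follows from the article alone and does not alter the arm estimate, but the rule needs an exception that the text does not give.

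For fidelity, the usual AR(1) rests on an unsupported assumption about variance and correlation across the start of training. For SD ratios of 0.5 to 1.25, the error of a POST-only test runs from about 13% to 3% with complete data. With 30% dropout the range is about 14% to 2.5%. It is nil at equal SDs and reverses if PRE is the more variable occasion. The PRE-to-POST contrast stays near nominal, with 8.4% as its worst case (SD ratio 0.5 and 30% dropout). All of these sizes rest on assumed SDs and correlations. No bias in the arm estimate and no sample-size error is shown. This is a cheap improvement, not a flaw that threatens the trial.

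**What to change.** Replace the AR(1) sentence in the general data analytic plan with, for example: the covariance of repeated measures within provider/child will be unstructured over the scheduled occasions, with no separate provider/child random intercept and with program/district random effects retained; if this model does not converge, a heterogeneous-variance AR(1) structure will be used.

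The cost is small. An unstructured covariance has 3 parameters for two occasions and 6 for three, against 2 for AR(1) alone: 3 − 2 = 1 extra for the child outcomes and 6 − 2 = 4 extra for fidelity, with about 590 providers planned. The sample size, the measurement schedule and the Time x Group comparison need no change.

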
#### Specific analyses for aim 1: test the effectiveness of the TEAMS modules individually and in combination on implementation outcomes when paired with two ASD EBI

To determine if there are significant main effects and interactions between the TEAMS groups on observed therapist fidelity (based on video recorded sessions coded at 3 time points over 6 months), statistical analyses will proceed using the 3-level nested data structure outlined in the General Analytic Plan section. To determine if there are significant differences between the TEAMS groups on observed child behaviors during sessions, statistical analyses will proceed using the 3-level nested data structure outlined in the General Analytic Plan section. To determine if there are differences between the TEAMS groups on child symptoms (EBCI or PDDBI) at 6 months, the 3-level nested data structured will be used.

#### Specific analyses for aim 2: test the impact of TEAMS modules on leader- and provider-level mechanisms of change

Measurement of leader-level outcomes is of primary interest. Implementation Leadership and Climate scores will be aggregated to the leader level. For this reason, HLM models (or single-level regression models if ICC values suggest clustering is negligible) will be used to test for TEAMS group differences on measures of implementation leadership and climate scores at 6 and 12 months. These analyses will control for baseline scores on these measures. To determine if there are significant differences between the TEAMS groups on therapist attitudes (EBPAS), analyses will proceed using the 3-level nested data structure outlined in the General Analytic Plan. These analyses will control for baseline EBPAS scores.

#### Specific analyses for aim 3: identify moderators and mediators of implementation outcomes

Variables representing participant characteristics (e.g., job tenure, gender, race/ethnicity) and organizational characteristics (e.g., size) will be evaluated as moderators of the relationship between the dummy-coded TEAMS group variables and outcome variables specified in aim 1. All analyses will proceed as specified in aim 1 above. Relevant interaction terms between the TEAMS group variables and a given moderator will be created and entered as predictor variables. Two sets of models will be used: one set for provider-level outcomes and a second for child-level outcomes. To examine the hypothesized mediated effects of TEAMS group status on fidelity and child outcomes, multilevel path analysis will be conducted. Measures of provider attitudes, implementation leadership and implementation climate will be tested as mediators in respective models. The specific mediated effects within these models will be tested using the bias-corrected bootstrap approach [108].

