#### Provider attitudes

Provider attitudes toward EBI have been linked to practice behavior [66, 67] and have been shown to predict use of EBI [13, 68, 69]. Multiple studies have found that provider attitudes before EBI training, especially openness to the use of EBI and perceptions of EBI appeal, are linked to fidelity after training [13, 70–72]. Furthermore, attitudes toward a specific practice are linked to reported use of that practice [69]. Negative beliefs about a practice may be a barrier to adoption [73, 74]. Data indicate that this may be especially true of behavioral interventions for ASD; however, poor attitudes can be improved with education [75, 76]. These studies, combined with preliminary data from the AIM HI and CPRT effectiveness trials linking attitudes toward ASD EBI and fidelity, indicate that provider attitudes are a promising and important target of implementation interventions aimed to increase uptake.

Therefore, the TEAMS Individual Provider Strategy (TIPS) for training applies well-established motivational enhancement strategies to motivate and engage providers in EBI training. Motivational interviewing (MI) [77–85] is a provider interaction style developed to address ambivalence about behavior change. MI is effective in facilitating behavior change for a wide-range of patient populations, improving treatment participation, attendance, adherence, and patient outcomes in a variety of treatments [86], including behavioral interventions [87]. Although MI is well-established for improving adult and adolescent *client* attitudes and engagement, there is limited application to enhance *provider* EBI training [73]. TIPS uses Miller’s conceptual model and clinical guidelines [88] for MI which emphasize AIM HI and CPRT trainers’ using an empathic learner-centered training style while evoking and strengthening the providers’ motivations for overcoming ambivalence about change (i.e., using AIM HI or CPRT). We will use the well-studied processes of MI in the TIPS module to improve provider attitudes and increase provider engagement in EBI training with the expectation that this will lead to improved EBI training completion, EBI fidelity, and child-level outcomes.

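### The aim 3 mediation models do not require baseline adjustment, so a module that shifts attitudes can be credited with working through them well above the nominal 5% rate

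*Protocol article*

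**What the plan says.** On mediation, the aim 3 analysis section of the protocol article states: "To examine the hypothesized mediated effects of TEAMS group status on fidelity and child outcomes, multilevel path analysis will be conducted". It adds: "Measures of provider attitudes, implementation leadership and implementation climate will be tested as mediators in respective models". The mediated effect is tested with a bias-corrected bootstrap. No baseline covariate is named for these models. The same section refers back to aim 1 for its moderator analyses, and the aim 1 section requires no baseline adjustment either.

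The general plan for aims 1-3 has the only overall rule: "Covariates (e.g., baseline scores) may be included in the models to adjust for nonequivalence at baseline and to minimize bias". The aim 2 section differs. For leadership and climate it requires control for baseline scores, and for provider attitudes it says "These analyses will control for baseline EBPAS scores".

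The background section on provider attitudes reports that "provider attitudes before EBI training, especially openness to the use of EBI and perceptions of EBI appeal, are linked to fidelity after training". Table 3 shows attitudes collected at PRE, leadership and climate at BL and PRE, and fidelity at PRE. The Sample section says that the aim 3 mediation analysis set the sample size.

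**The concern.** Only the TEAMS group is randomised. The step from POST attitudes to fidelity compares providers whose attitudes differ for many reasons, including the attitudes they held before training. If those earlier attitudes also bear on later fidelity by another route, POST attitudes and fidelity will correlate even when changing attitudes does nothing. A module that moves attitudes then appears to work through them.

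Balance between arms does not help. With perfectly balanced arms, the mediator-to-outcome path is just as confounded. A rule that makes adjustment optional, with imbalance at baseline as its leading reason, can therefore leave the adjustment out exactly where it is needed. At stake is the mechanism conclusion of the aim for which the trial was sized.

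**Working it through.** **1. The plan's own figure.** The Power analyses section gives VIF = 1 + (8 − 1) × 0.04 = 1.28 and R² = 2% for both mediator and outcome, and arrives at 591 providers.
- 591 / 1.28 = 462 independent providers.
- A simple module-mediator-outcome model with both paths √0.02 = 0.141 and a two-sided 5% bias-corrected bootstrap has simulated power 0.819 at n = 462.
- 462 × 1.28 = 591, and 591 / 8 rounds up to 74.

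The figure reproduces from a model with no baseline covariate. That is consistent with an unadjusted analysis but does not prove one is planned.

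**2. False-mediation rate, unadjusted.** Assumptions:
- POST attitudes have no effect on fidelity.
- The module shifts attitudes with R² = 2% (d = 2√(0.02/0.98) = 0.286).
- PRE and POST attitudes correlate at s (assumed 0.5-0.7).
- PRE attitudes correlate with POST fidelity at r by a route other than POST attitudes (assumed; the documents give no size).
- Two equal groups, TIPS versus no TIPS.
- Mediation is declared when both paths have p < 0.05. This stands in for the bootstrap and is somewhat conservative: at n = 462 its power for the plan's mediated effect is 0.75, against 0.82.

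Rate ≈ Φ(√(0.02/0.98)·√n − 1.96) × Φ(sr/√(1 − s²r²)·√n − 1.96).

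With full retention, n = 462. With the 30% attrition used in the aim 1 calculation, n = 590 × 0.7 / 1.28 = 323. The first factor is 0.87 and 0.73 respectively.

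| s | r | n = 462 | n = 323 |
|---|---|---|---|
| 0.5 | 0.10 | 16% | 11% |
| 0.5 | 0.14 | 28% | 18% |
| 0.6 | 0.10 | 22% | 14% |
| 0.6 | 0.14 | 38% | 24% |
| 0.7 | 0.10 | 28% | 18% |
| 0.7 | 0.14 | 49% | 31% |
| 0.5 | 0.20 | 50% | 32% |
| 0.6 | 0.20 | 64% | 42% |
| 0.7 | 0.20 | 74% | 52% |

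The rate reaches 50% at r = 0.20, 0.17 and 0.14 for s = 0.5, 0.6 and 0.7 with full retention. With 30% attrition it does so at r = 0.27, 0.22 and 0.19. Direct simulation (4,000 trials per cell) agrees with the table to within about 2 points.

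**3. Check with clustering.** The setting was 74 × 8 providers, ICC 0.04, 30% attrition, cluster-robust errors, Monte Carlo intervals for the mediated effect, s = 0.6 and 400 trials per cell. The rates were 13% at r = 0.08, 27% at 0.14, 52% at 0.22 and 75% at 0.32.

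**4. Single-arm dummy contrasts.** The general plan codes four groups with three dummies. For TIPS versus standard the first path has about 462/4 = 115 independent providers per arm, or 323/4 = 81 with attrition. Its power, Φ(0.286/√(2/115) − 1.96) = 0.58, or 0.44 at 81 per arm, caps the false-mediation rate. At s = 0.6 and r = 0.14 the rate is 26%, or 15% with attrition.

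**5. After adjustment.** With PRE attitudes in both equations the rate is about 4-5% in the two-group simulation and 4-7% in the clustered one, where the latter also covers larger module shifts. PRE attitudes in the mediator equation alone, which is what carrying over the aim 2 rule would give, does not help: the clustered rates stay at 17% or more.

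**The case against.** The strongest reply is that a journal article may leave the covariates of a mediation model to a fuller plan, that nothing here forbids adjustment, and that the general rule also cites minimising bias as a purpose. All of that is true, and a reader who inferred that the plan rules out adjustment would be wrong. But the article is not merely silent. It makes baseline scores optional for all aims and makes them mandatory for aim 2 alone, so an unadjusted mediation model complies with it.

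Second, a link between earlier attitudes and later fidelity need not be confounding. If it runs entirely through POST attitudes, there is no bias. That stands as a condition on the result. The documents do not establish either route, and adjustment guards against the harmful one.

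Third, a reader might infer that false mediation would be the usual result. The documents do not support this: they give no correlation between PRE attitudes and POST fidelity, and at small correlations the rate is mostly well under one half.

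Fourth, a reader might infer that the protocol also states that PRE fidelity predicts later fidelity. It does not. The nearest text is the power calculation "using an autocorrelation value of 0.60", a planning assumption. If fidelity enters the path model as a repeated outcome that includes PRE, this part is already partly handled; the aim 3 section does not say.

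Fifth, requiring PRE provider scores in every model would be unsafe. The TLI paragraph places the first leader workshop before provider enrollment and pre-assessment, so in the TLI arms those scores may already carry some of the module's effect. This objection stands and shapes the fix.

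**Conclusion.** The concern holds in a limited form. The plan allows mediation models without baseline scores, and its own background names a variable that may confound the mediator-to-outcome path. Under the stated assumptions the false-mediation rate for a two-group TIPS contrast is about 11-49% at r = 0.10-0.14, against a nominal 5%. It exceeds one half only at about 0.2 or more (0.14-0.20 with full retention and 0.19-0.27 with 30% attrition, depending on attitude stability). It is lower for single-arm dummy contrasts.

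The attitude stability, the size of r and the route outside POST attitudes are assumptions, not figures from the documents. The percentages concern attitudes as mediator. For leadership and climate the same reasoning applies, but no rate was computed. The point should be settled before mediation results are seen, because it affects the mechanism claim of the aim that set the sample size.

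**What to change.** State in the aim 3 analysis section, to apply whether or not arms differ at baseline:

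- Attitude-mediation models for the TIPS contrasts include PRE attitudes in both the mediator and the outcome equation.
- Leadership and climate mediation models include the BL score of the mediator in both equations.
- The outcome equation includes PRE fidelity, or the PRE child measure, unless it is already modelled as a repeated outcome.
- Study is included in every model.
- For TLI contrasts, results are reported with and without PRE provider scores, as a sensitivity analysis, because those scores follow the leader workshop.

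All these variables are already collected. The cost is a change of analysis wording and slightly less precision on the mediator-to-outcome path.
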